### Randomization

Following screening and health examinations, we enroll candidate participants and researchers who are not involved in interventions or tests that are sensitive to blinding randomize them using the open-source minimization program MinimPy 0.3 [58, 59]. To ensure even distribution of subjects throughout the study period, we decided to employ a stratified, biased coin minimization with 0.95 base probability and to use allocation ratios corresponding to the group sizes (see Statistics and power calculations section below). Participant stratification is based on a 30-second chair-stand test (<16 or ≥16) and on gender to ensure equal allocation to one of the five intervention groups and further to determine if the participant will participate in invasive acute mechanistic MPS trials (see Muscle protein synthesis section below), as demonstrated in Fig. 3.

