### Statistics and power calculations

For all power calculations, we will apply a level of significance of 0.05 and a power of 0.80, and the primary outcome is the degree of muscle hypertrophy determined as the change in quadriceps muscle CSA on MRI scans over the course of the 12-month intervention. On the basis of previous data [91], we set the following parameters: least average expected change over the course of the 12-month intervention between distinct intervention groups, 300 mm^2^ (corresponding to an estimated relative change of 6.5 %) with a SD set to 140 mm^2^. Our goal is to be able to detect differences between groups’ mean hypertrophy down to approximately 2 %, which corresponds to approximately 80 mm^2^. A difference in the change of quadriceps muscle CSA greater than 80 mm^2^ between any two groups is statistically detectable with a power of at least 0.80 with a group size of 30. We decided to include 35 subjects in each of the three groups (HRTW, LITW, and CARB), as we anticipated a dropout rate of 15 % at the time of study initiation. In the WHEY and COLL groups, we expected a larger dropout rate because of taste issues with protein supplements and no motivational effect by training as in the HRTW and LITW groups. Thus, we will include 50 each in the WHEY and COLL groups. On an ad hoc basis, we will evaluate the actual dropout rate and adjust the total number of inclusions accordingly.

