In a subset of participants from the five intervention groups, we will conduct experimental tracer studies before and after the 12-month intervention period to determine the extent to which the interventions affect the responsiveness of MPS to protein intake. The goal is to measure whether any of the interventions enhance the anabolic sensitivity to protein intake and thereby investigate if we can link the observed differences in muscle mass over the course of the intervention period to changes in the anabolic response to protein feeding. Thus, the outcome measure is the relative change in the FSR of muscle proteins from the basal condition, defined as the overnight fasted and resting state, to the average 4-h postprandial period after intake of a standard protein bolus. We are not aware of any data on changes in MPS responsiveness over time, and we therefore based the power calculations on a sum of our own published and unpublished data obtained in healthy elderly participants. We established the following parameters: expected average 4-h postprandial responsiveness to protein feeding from basal condition of 0.016 %/h (i.e., approximately corresponding to an increase in muscle protein FSR of 50 %) with an interparticipant SD on the increase of 0.017 %/h. We aim to be able to detect a 50 % change in responsiveness within a group over the course of the 12-month period (i.e., a change of 0.008 %/h in the increase in the muscle protein FSR from 0.016 %/h to 0.024 %/h). The SD for the change in responsiveness is set as 0.006 %/h. By including 10–12 participants, we obtain a power of at least 0.80 to detect a statistical difference over time within each intervention group. By taking the probability of dropouts into account, we decided to include 12 participants in the HRTW, LITW, and CARB groups and 15 in the WHEY and COLL groups, respectively.

Investigators will analyze data as intention-to-treat (except in subgroup analyses) as well as per protocol, and we will test the following groups against each other using one-way analysis of variance of the relative group changes from baseline to 12 months: (1) WHEY vs. COLL vs. CARB and (2) HRTW vs. LITW vs. WHEY. We will not conduct any interim analyses in this project.

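### The primary test is an unadjusted one-way ANOVA of relative CSA change: it leaves out the minimisation factors and baseline CSA, and the planning SD is given only in mm²

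*Protocol article*

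**What the plan says.** **Test.** The Statistics and power calculations section names a "one-way analysis of variance of the relative group changes from baseline to 12 months", run twice on three groups: WHEY, COLL and CARB, then HRTW, LITW and WHEY. It names no covariate.

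**Allocation.** Under Randomization, participants are allocated by biased-coin minimisation with base probability 0.95. "Participant stratification is based on a 30-second chair-stand test" (below 16, or 16 and above) and on gender. Information and screening adds that this screening test serves stratified randomisation only. Nothing in the article brings either factor into the analysis.

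**Outcome and sizing.** For the power calculation the primary outcome is "determined as the change in quadriceps muscle CSA on MRI scans over the course of the 12-month intervention", without the word relative. The expected change is "300 mm^2^ (corresponding to an estimated relative change of 6.5" per cent), "with a SD set to 140 mm^2"². The smallest difference of interest is "down to approximately 2 %, which corresponds to approximately 80 mm^2"². No SD is given in per cent.

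**Baseline.** Table 3 schedules the MRI CSA at baseline and at 12 months, so baseline CSA is available for every participant who is scanned.

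**The concern.** There are two separate issues.

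**Precision.** Minimisation balances the arms on gender and chair-stand class, which reduces the real sampling variance of the arm differences if those factors predict the outcome. A one-way ANOVA leaves the variance they explain in the residual, so its standard error does not reflect that reduction. The test then rejects less often than its nominal level, and precision gained by the design is not used. Baseline CSA is not a minimisation factor, so leaving it out does not disturb the type I error, but precision is lost if it predicts the outcome.

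**Scale.** Mean mm² change and mean percentage change are different summary measures whenever baseline muscle size varies. Planning inputs in mm² carry over to a test in per cent only with an SD on the percentage scale or a stated common baseline. The article gives neither.

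**Working it through.** **1. The plan's own conversions.**
- 300 mm² = 6.5 %: implied baseline 300 / 0.065 = 4615 mm².
- 80 mm² = 2 %: implied baseline 80 / 0.02 = 4000 mm².
- At 4615 mm², 80 mm² is 80 / 4615 = 1.7 %, and 2 % is 0.02 × 4615 = 92 mm².
- The SD of 140 mm² becomes 140 / 4615 = 3.0 % or 140 / 4000 = 3.5 %, and only if baseline is treated as the same for everyone.
- The standardised target is 80 / 140 = 0.57 if 80 mm² is meant, and 92 / 140 = 0.66 if 2 % of 4615 mm² is meant.

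The stated 30 per group does not follow from 80 and 140 mm² either: 2 × (1.96 + 0.84)² × 140² / 80² gives 49 two-sided. That is a separate sample-size question, and nothing below depends on it.

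**2. Two scales, two targets.** Assume baselines of 5200 mm² in men and 4000 mm² in women (the article gives none). A uniform gain of 80 mm² is then 1.5 % in men and 2.0 % in women. With 5600 and 3600 mm² it is 1.4 % and 2.2 %. The percentage scale gives the same mm² gain more weight in people with smaller muscles.

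**3. Standard error.** Let R² be the share of outcome variance explained by gender and chair-stand class. It is not in the article, so a range is used. Under balance the unadjusted standard error is too large by 1 / √(1 − R²):

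| Assumed R² | Factor |
|---|---|
| 0 | 1.00 |
| 0.05 | 1.03 |
| 0.10 | 1.05 |
| 0.20 | 1.12 |

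**4. Type I error and power by simulation.** Set-up: 205 participants; allocation 35/35/35 (HRTW, LITW, CARB) and 50/50 (WHEY, COLL); minimisation with a 0.95 coin on two binary factors, each split evenly and contributing equally (assumed); total SD 140 mm²; no dropout; 2000 trials with both three-group tests, so 4000 tests per row. Power is for one arm shifted by 80 mm². The adjusted model contains the two factors only, not baseline CSA.

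| Assumed R² | Type I, unadjusted | Type I, adjusted | Power, unadjusted | Power, adjusted |
|---|---|---|---|---|
| 0 | 0.051 | 0.051 | 0.76 | 0.77 |
| 0.05 | 0.041 | 0.048 | 0.75 | 0.77 |
| 0.10 | 0.035 | 0.048 | 0.77 | 0.81 |
| 0.20 | 0.026 | 0.051 | 0.78 | 0.86 |

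The simulation error of a rate near 0.05 is about √(0.05 × 0.95 / 4000) = 0.003.

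**5. Check by formula.** In large samples with exact balance, a three-group test has true level 0.05^(1/(1 − R²)). This gives 0.043, 0.036 and 0.024 for R² of 0.05, 0.10 and 0.20, in line with the simulation.

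**The case against.** - **The plan is valid as it stands.** True: the error is conservative. A reader might infer inflated false positives, but the type I error only falls.
- **The loss may be nil.** Also true. No figure in the article shows that gender or chair-stand class predicts CSA change, and dividing by baseline may already remove part of any gender difference. A reader might take it as fact that the standard errors are too large; the documents support only the conditional statement.
- **The target is stated in per cent.** It is, with 80 mm² offered as its equivalent. So one cannot say that the sample size refers to a different quantity from the one tested. What stands is narrower: no percentage-scale SD is given.
- **The two implied baselines may be rounding.** Possibly: 1.7 % can be called approximately 2 %. That weakens the inconsistency but does not supply the missing SD.
- **Relative hypertrophy is a coherent target.** Agreed. The point is to use one scale throughout, and a log model keeps a relative effect.
- **This is detail for the SAP.** Not here: the article positively names a model without covariates. By contrast, which pairwise contrasts follow the three-group test is commonly left to a SAP, and the article already speaks of detecting differences between any two groups. A reader might object that an omnibus F cannot establish that whey is superior to each comparator, but the missing contrasts are not a fault of this document.

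**Conclusion.** The point holds as a free improvement in precision and clarity, not as a threat to validity.

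**Precision.** The size depends wholly on an R² that the article does not give. At 0.05 to 0.10 the standard error is overstated by about 3 to 5 %, type I error is about 0.041 to 0.035, and simulated power is lower by roughly 0.02 to 0.04. At 0.20 the overstatement is about 12 % and type I error about 0.026. At zero, adjusting costs nothing. These figures assume evenly split factors and no dropout, and they leave out any further gain from baseline CSA.

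**Scale.** The stated power refers to an SD in mm² and is not established for a percentage-change test.

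**Limits.** Leaving covariates out of a linear model does not change the estimand; only the choice between mm² and per cent does. Nor should adjustment be read as repairing the sample size: with the adjusted SD, the number needed per group for 80 mm² is still 46, 44 and 39 at R² of 0.05, 0.10 and 0.20.

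**What to change.** 1. Choose one scale and use it for outcome definition, sizing and test. In mm², the SD of 140 and the difference of 80 can stay, with per cent reported descriptively. If a relative effect is wanted, state an SD on that scale and a single baseline for the conversion. If relative was not meant as percentage change, correct the word.
2. Replace the one-way ANOVA with an ANCOVA of 12-month quadriceps CSA in mm² on arm, baseline CSA, gender and chair-stand class (below 16, or 16 and above, as used at allocation). For a relative effect, use log 12-month CSA with log baseline CSA; the arm effect is then a ratio.
3. Record this in the protocol and SAP before the final analysis. The article reports 153 randomised and 54 through the intervention, with no interim analysis planned, so at that date it could still be pre-specified.

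**Cost:** one model statement and one sentence on scale. All covariates are already collected, and no participant or visit is added. Three covariates use three residual degrees of freedom: 117 to 114 in the HRTW, LITW and WHEY test (120 planned), and 132 to 129 in the WHEY, COLL and CARB test (135 planned).

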## Discussion

The inclusion rate is currently 15 %, and we have been in contact with more than 1000 elderly individuals, recruiting approximately 150 participants. The major challenge until now has been to find elderly individuals who are willing to be committed to participate for 18 months as well as accept the outcome of the randomization. The interventions are very different in terms of time required for the intervention as well as potential physical and social gain. The three supplementation-only groups demand less time, but the candidates expect less gain from the intervention than those in the more time-consuming physical training groups, so the main reasons for candidates to decline participation is the uncertainty of the randomization. This has resulted in roughly 45 % of candidates having decided to refrain from volunteering. Second, our exclusion criteria are numerous in order to ensure accurate results, and we have excluded around 40 % of the potential participant population for this reason, leaving for inclusion 15 % of those who had initially contacted us. The invasive procedures and number of tests are not issues of major importance for the participants when we are recruiting. Fortunately, the dropout rate until now has been very low: Only 4.3 % have ceased participation, which is far less than the initially expected rate of 10–15 %. We recruit research participants for this study in the Capital Region of Denmark. The population in this region is wealthier [92], and likely also healthier, than the general population in Denmark, but for practical reasons we could only recruit participants locally. This represents a possible selection bias in the trial.

### Safety issues and dropout rate

We consider the project safe, and the clinical staff routinely perform the tests and invasive procedures used. We supervise participants during heavy strength training and carefully instruct them in the light load training exercises. The nutrient supplements contain 510 kJ (i.e., a dose of 1020 kJ/day) and induce mild satiety when ingested. Therefore, we expect a slight decrease in the participants’ habitual diet corresponding to the energy content in the supplements, and we expect their body weight to be stable. We control HbA1c, creatinine, and cholesterol levels after 6 months to ensure that participants do not develop insulin resistance, impaired kidney function, or hyperlipidemia because of supplement intake. In case of adverse events, the Danish Patient Compensation Association covers participants’ treatment needs.

### Perspectives

The purpose of the CALM Intervention Study is to provide interdisciplinary knowledge on the efficacy and feasibility of daily protein supplementation and muscular exercise training in different settings to support the maintenance of skeletal muscle mass in the elderly to ensure daily functional capacity and maintain or improve quality of life. Until now, only a few studies have investigated the physiological outcome of strength training and protein supplementation, and, to our knowledge, a light intensity strength training regime has never been investigated. Further, the interdisciplinary setting, including sensory, fecal, and qualitative investigations, will provide unique insights into how to counteract the age-related loss of skeletal muscle mass.

A key assumption in the CALM Intervention Study is that an improved adherence to a healthier lifestyle requires sensitivity to the everyday lives, routines, and cultural differences of the research participants [93]. We aim to enhance this sensitivity by gathering qualitative knowledge on the societal, cultural, and individual factors that influence daily routines related to nutrient consumption and exercise to identify and circumvent the barriers that complicate changes in these. We will perform an exploration of societal and individual influences on everyday lifestyle habits and of how the project configures the participants’ everyday food and exercise practices. Further, we will investigate how participants’ practices are (and are not) transformed by their interactions with the materiality as well as the scientific practitioners and attitudes of the project to provide insights that potentially could improve health promotion strategies [94].

We expect to translate the results of this into guidelines targeted to the home-dwelling, independent elderly population and disseminate them to the public through channels involving nongovernmental organizations, newspapers, electronic media, and stakeholders in, for example, the municipalities. The CALM Intervention Study will provide novel information on the potential longitudinal benefits of protein supplementation and strength training regarding physical performance, gut microbiota, and overall health while taking into account the feasibility and impact of the interventions on everyday life.

### Trial status

Since we began advertising for participants in January 2014, we have recruited and randomized 153 (as of 1 August 2016). A total of 54 and 32 participants have completed the intervention and follow-up, respectively.

## Abbreviations

CALM, Counteracting Age-related Loss of Skeletal Muscle Mass; CARB, carbohydrate supplementation group; COLL, collagen supplementation group; COPD, chronic obstructive pulmonary disease; CSA, cross-sectional area; DXA, dual-energy X-ray absorptiometry; EULAR, European League Against Rheumatism; FEV_1_, forced expiratory volume in 1 second; FSR, fractional synthesis rate; FVC, forced vital capacity; GC-TOF-MS, gas chromatography with time-of-flight mass spectrometry; GOLD, Global Initiative for Chronic Obstructive Lung Disease; HRTW, heavy resistance training with whey supplementation; ITS, internal transcribed spacer; K_3_-EDTA, tripotassium ethylenediaminetetraacetic acid; LITW, light-intensity training with whey supplementation; LVEF, left ventricular ejection fraction; MPS, muscle protein synthesis; MRI, magnetic resonance imaging; NMR, nuclear magnetic resonance; OGTT, oral glucose tolerance test; PDCAAS, protein digestibility-corrected amino acid score; PSQI, Pittsburgh Sleep Quality Index; RCT, randomized controlled trial; RM, repetition maximum; ROI, region of interest; SF-36, 36-item Short Form Health Survey; SPIRIT, Standard Protocol Items: Recommendations for Interventional Trials; SWFL, Satisfaction with Food-related Life scale; WHEY, whey supplementation
